## Abstract

International students face elevated risk for mental health problems and suicide, yet encounter multiple barriers to accessing timely and culturally responsive treatments. Key challenges include high rates of psychological distress, low mental health literacy, and reduced help-seeking, often compounded by perceived burdensomeness, a lack of belonging, and difficulties with emotion regulation. Bud is a self-guided, co-designed mobile app developed to address these challenges through an accessible digital intervention. This paper outlines a protocol for a randomized controlled trial evaluating the effectiveness, acceptability, engagement, and safety of Bud among international students enrolled at Australian tertiary institutions. The trial also includes an internal pilot phase to ensure the feasibility of the trial procedures, with benchmarks for recruitment, retention, and engagement. A community sample of 302 participants will be randomly assigned to either the intervention group (Bud app) or the active control group (online mental health fact sheets) for four weeks. Assessments will be completed online at baseline, two weeks, and four weeks post-baseline. The primary outcome is psychological distress, with secondary outcomes including help-seeking intentions, perceived burdensomeness and belonging, emotion regulation, mental health literacy, and suicidal ideation. Acceptability and engagement will be assessed using self-report and objective measures. Interviews will be conducted with a subset of 20 participants to explore their views on Bud further. This trial will provide the first evaluation of a suicide prevention tool specifically for international students. If effective, Bud could offer a scalable and culturally relevant solution to improve student mental health and reduce service access barriers.

**Trial registration:**

ACTRN12625000584437.

## Background

1

Suicide is a leading cause of death for young people aged 15–29 [1], and rates are particularly elevated in students enrolled in tertiary education, such as university or college [2]. International students comprise a significant proportion of tertiary education populations globally [3], yet they face unique challenges that can adversely affect their mental health [4]. Although past-year rates of suicidal ideation and self-harm are similar between international and domestic students (5.6–9.8 % vs. 5.2–13.3 % for ideation; 4.3–17.2 % vs. 3.2–22.9 % for self-harm), international students report higher rates of suicide attempts (1.21–2.2 % vs. 0.1–1.6 %) [5]. This elevated risk for severe outcomes appears to be driven by a complex interplay of stressors, including academic pressure, acculturative stress, and stigma [5].

Despite growing awareness of these risks, most suicide prevention still depends on traditional support, such as clinical treatment through health services or generic mental health information delivered universally by educational institutions [6]. There are two key limitations to these standard approaches. First, international students, including those who die by suicide, are less likely to engage with health services because of barriers such as stigma, visa concerns, low mental health literacy, and high treatment costs [[7], [8], [9], [10]]. Second, students who seek support often find services difficult to access when needed, poorly adapted to their cultural context, or mismatched to their expectations, leading to disengagement [11,12]. These findings highlight a clear need for suicide prevention strategies that are developed *with* and *for* international students and delivered in ways that are timely, relevant, and accessible [13].

Digital interventions targeting modifiable risk and protective factors for suicide represent a promising avenue for suicide prevention with international students [13,14]. They can offer scalable, low-cost, and on-demand support that overcomes key barriers to help-seeking and treatment utilization, particularly for culturally and linguistically diverse populations [14,15]. Evidence suggests that digital programs can improve mental health literacy, reduce stigma, enhance self-regulation skills, and, in some cases, directly reduce suicidal ideation [15,16].

A growing number of such programs have demonstrated short-term benefits in university settings. Universal interventions, such as online gatekeeper training (e.g., *ASK About Suicide*, *Kognito*), improve suicide-related knowledge and preparedness but have shown mixed effects on behaviour and are rarely tailored to the needs of diverse student groups [17,18]. Selective and indicated interventions like *eBridge* and *LifeBuoy* have demonstrated improvements in help-seeking and reductions in suicidal ideation among students with elevated risk [19,20]. However, existing programs have largely overlooked international students, despite their heightened vulnerability and well-documented barriers to engaging with support services [6].

We sought to address this gap through the development of *Bud*, a co-designed mobile app grounded in evidence-based therapeutic approaches and informed by best-practice recommendations for proactive engagement and risk screening [6]. Developed in collaboration with international students, the app is designed to be accessible, non-stigmatizing, and aligned with the common experiences and challenges faced by this population, such as academic pressure, social isolation, and acculturative stress [21,22]. Cultural responsiveness was embedded through a structured co-design process with international students, ensuring that the app's content, tone, and delivery reflected their lived experiences, preferences, and values. This included avoiding clinical language, incorporating personal narratives, and designing flexible, self-guided tools that align with students' needs and challenges.

Informed by this process, Bud functions as a community-level intervention that targets modifiable risk and protective factors associated with suicide through a suite of brief, interactive tools, personal stories, and skills-based modules. Rather than addressing a single diagnosis, *Bud* adopts a transdiagnostic approach by targeting shared mechanisms that underlie psychological distress, suicidality, and related mental health challenges [23,24]. At its core is an emotion-tracking feature that facilitates emotional self-awareness and recommends contextually appropriate support tools, consistent with the principles of just-in-time adaptive interventions [25]*.* The tools draw on cognitive behavioural (CBT), dialectical behavioural (DBT), and acceptance and commitment (ACT) therapies to reduce psychological distress, strengthen emotion regulation, and support values-based coping strategies associated with reduced suicidal ideation [16,26].

To address interpersonal risk factors such as perceived burdensomeness and thwarted belonging [27]*,* the app includes activities informed by evidence-based strategies such as self-compassion, values reflection, and small social actions that promote connection [28]*.* Help-seeking is indirectly supported through stories from international students sharing their lived experiences of studying, living abroad, and navigating suicidal thoughts. These narratives aim to normalise help-seeking and validate users’ emotional experiences. Evidence suggests that suicide prevention narratives featuring peer experiences of coping and recovery can increase help-seeking intentions, reduce suicidal ideation, and foster identification with the storyteller, particularly among young people [29]*.* Additionally, Bud features a brief, peer-support-focused gatekeeper module aligned with non-Western adaptations [30,31] that equips students with the skills to recognise potential suicidal ideation in others and respond effectively. This component was developed in response to co-design feedback indicating that while many students were reluctant to engage with suicide-specific content for themselves, they were open to learning how to help others.

The selection of outcomes for this trial was guided by Bud's theory of change and its positioning as a community-level suicide prevention intervention. Designed to support international students across the continuum of psychological distress, Bud delivers evidence-based skills that address upstream risk and protective factors for suicide, offering early intervention for those not yet experiencing suicidal thoughts, and meaningful support for those who are. Accordingly, psychological distress was selected as the primary outcome due to its high prevalence in this population (with approximately 50 % reporting moderate to severe distress) [32,33], its robust association with suicidal thoughts and behaviours [34], and its demonstrated responsiveness to low-intensity self-guided digital interventions [35,36].

The secondary outcomes were selected to capture key suicide-related risk and protective factors targeted by the intervention. Help-seeking intentions were assessed due to consistent evidence that international students, including those who die by suicide, are often reluctant to engage with mental health services [8,9]. Perceived burdensomeness and sense of belonging were included based on their established associations with suicidality [37,38] and high relevance to international students, who frequently report experiences of academic underperformance, isolation, and cultural disconnection [4,5]. Suicidal ideation was included as a core suicide-related outcome to assess the app's impact on direct indicators of suicide risk. Mental health literacy was included because it supports symptom recognition, self-care, and help-seeking, and is often lower among international students compared to domestic peers [9,39]. Emotion regulation was included as a hypothesised mechanism of change, given its established link to reduced suicidal thoughts and behaviours [40]. This construct is targeted through several app features, including the emotion tracking and recommendation system, which aim to strengthen students' capacity to manage distress in the moment.

This study will evaluate the effectiveness, acceptability, engagement, and safety of Bud, a co-designed digital suicide prevention app for international students (see Table 1 for a summary of the study aims and hypotheses). The primary aim is to determine whether Bud leads to greater reductions in psychological distress compared to an active control condition. The secondary aims include evaluating whether Bud leads to improvements in suicide-related risk and protective factors, including help-seeking intentions, perceived burdensomeness, sense of belonging, emotion regulation, and suicidal ideation. The study will also assess the app's acceptability, monitor for any iatrogenic effects, and evaluate user engagement using self-report and app-derived metrics. An embedded internal pilot phase will assess the feasibility of trial procedures, with predefined benchmarks for recruitment, retention, and intervention engagement. Interviews will be conducted with a subset of participants to further explore their views on Bud's acceptability, usability, and opportunities for implementation.

**Table 1 tbl1:** Study aims and hypotheses.

Aims	Hypotheses
**Aim 1:** To evaluate the effectiveness of *Bud* compared to an active control condition on psychological distress and suicide-related risk and protective factors	***Primary outcome***
	*H1:* Participants using *Bud* will report greater reductions in psychological distress compared to the control group at post-intervention.
	***Secondary outcomes***
	*H2:* Participants using Bud will report greater increases in help-seeking intentions compared to the control group at post-intervention.
	*H3:* Participants using *Bud* will report greater reductions in perceived burdensomeness and thwarted belongingness compared to the control group at post-intervention.
	*H4:* Participants using *Bud* will report greater improvements in emotion regulation compared to the control group at post-intervention.
	*H**5**:* Participants using *Bud* will report greater increases in mental health literacy from the intervention than the control group.
	*H6:* Participants using *Bud* will report greater reductions in suicidal ideation compared to the control group.
**Aim 2:** To assess the acceptability of the Bud app among international student users	*H7:* Participants in the Bud group will rate the app as acceptable, including positive evaluations of its engagement, functionality, aesthetics, information quality, and overall subjective quality.
**Aim 3:** To assess engagement with the Bud app	*H8:* Participants in the Bud group will demonstrate high engagement, reflected in app usage metrics and perceived helpfulness of activities.
**Aim 4:** To assess the safety of the Bud app	*H9:* No iatrogenic effects (e.g., increases in suicidal ideation or psychological distress) will be observed or reported among participants in the Bud group.

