### Assessments

2.9

Assessments will be conducted remotely via REDCap (Research Electronic Data Capture [46,47]) at T1, T2, and T3 (see Table 2).A.*Descriptive Information.* Demographic variables collected at baseline (T1) will include age, gender, country of origin, time in Australia, nationality, education level, study area, degree level, self-rated English language proficiency, and current grade point average (GPA). In addition, participants will be asked to report on previous suicide attempts and considerations of attempts (past 12 months), self-harm behaviours (past 12 months), adjustment to university (College Adjustment Questionnaire: CAQ; [48]), and adverse childhood experiences (Adverse Childhood Experiences Checklist: ACEs [49]).B.*Outcomes.* Primary and secondary outcomes will be assessed at T1, T2 and T3.The primary outcome of this study is psychological distress measured with the Kessler Psychological Distress Scale (K10) [50]. This measure has been validated in diverse populations and is widely used in health related research [56]. Secondary outcomes will include key risk and protective factors for suicidal thoughts and behaviours targeted by the app, including help-seeking intentions using the General Help-Seeking Questionnaire (GHSQ [51]); Perceived burdensomeness and belonging using the Interpersonal Needs Questionnaire (INQ [52]); Emotion regulation using the Difficulties in Emotion Regulation Scale Short Form (DERS-SF [53]); Suicidal ideation using the Youth Suicide Ideation Screen–3 (YSIS-3 [57]); and mental health literacy with the Mental Health Learning Scale (MHL-9 [54]) adapted to refer to the interventions rather than school settings. All instruments are brief psychometrically validated tools designed for self-reporting and appropriate for digital intervention studies.C.*Acceptability and Iatrogenic effects.* Acceptability of the intervention will be assessed at T3 in the intervention group using the User Version of the Mobile Application Rating Scale (uMARS [55]) and a single general satisfaction item (e.g., how satisfied were you with the app?). To assess both acceptability and potential iatrogenic effects, participants in both trial arms will complete a custom measure previously used in suicide prevention research [58]. This measure captures perceived acceptability (e.g., whether the app or fact sheets were enjoyable or worthwhile) and potential iatrogenic effects (e.g., whether the content was upsetting or increased suicidal thoughts). Changes in suicidal ideation, along with monitoring of adverse events, will also provide additional insight into potential iatrogenic effects.D.*Engagement.* For the control intervention, the number of times the fact sheets are accessed will be recorded via REDCap. For the Bud intervention group, app usage data will be collected from participants to assess engagement and perceived usefulness of the Bud app. Specifically, this will include the total number of times the app is accessed, the number and type of activities completed, and responses to in-app prompts asking whether each activity was helpful. These metrics will quantify overall dosage and identify which features are most frequently accessed and perceived as most useful by participants. Participants will also have the opportunity to express interest in participating in an interview about their experience with the app.E.*Interview questions.* A subset of participants from the Bud intervention group who express interest will be randomly selected and invited to participate in online qualitative interviews conducted on Microsoft Teams. We will aim to recruit 20 participants. They will receive $30 for participating in an interview and will be asked to reflect on the app's design, usability, technical challenges encountered, and privacy and security concerns related to sharing personal information within the app. Additionally, the interview will explore the app's content regarding cultural appropriateness, relevance to their experiences as international students, their thoughts about how it could best be disseminated to international student populations, and suggestions for improvement.

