
**Table 2 tbl2:** Study measures at each time point.

Domain	Measure	# items	T1	T2	T3
Descriptive information	Demographic questionnaire	14	X		
	Previous Suicide attempts	2	X		
	Previous self-harm behaviours	1	X		
	Adjustment to University: CAQ [48]	14	X		
	Adverse Childhood Experiences: ACEs [49]	11	X		
Primary outcome	Psychological Distress: K10 (50)	10	X	X	X
Secondary outcomes	Help-Seeking: GHSQ [51]	12	X	X	X
	Perceived Burdensomeness: INQ [52]	5	X	X	X
	Sense of Belonging: INQ [52]	5	X	X	X
	Emotion Regulation: DERS – SF [53]	18	X	X	X
	Suicidal ideation: YSIS-3 (45)	3	X	X	X
	Mental health literacy: MHLS-9 (54)	9			X
Acceptability & iatrogenic effects	Open feedback question	1	X	X	X
	Acceptability and Iatrogenic effects: Custom Measure	6			X

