	***Intervention group only***				
	App usage (number and time accessing)	App metric		X	X
	Number and type of activities completed	App metric		X	X
	Perceive helpfulness of activities	In-app self-report		X	X
Total # of survey items per group			I = 96	I = 54	I = 92
			C = 96	C = 54	C = 69

Note: I = Intervention group, C = Control group. Each measure is described in detail below.

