#### Main analyses

2.10.2

Changes in the primary and secondary outcomes will be evaluated using generalised linear mixed models (GLMMs), including random intercepts for participants, random slopes for time, and fixed effects for group, time, and their interaction. For zero-inflated outcomes such as suicidal ideation (e.g., a large number of individuals reporting no ideation), model diagnostics will be used to assess the appropriateness of the GLMM approach, with consideration of alternative specifications (e.g., two-part models such as the zero-inflated Poisson model) if indicated [60,61]. Measures of acceptability and iatrogenic effects will be assessed with descriptive statistics. Pearson correlations will explore associations between app engagement and mental health outcomes. Exploratory analyses will investigate potential moderators, including demographics (e.g., gender and country of origin) and emotion regulation, for the primary and secondary outcomes, as well as for the engagement and acceptability measures. Sensitivity analyses will be conducted to assess whether outcome patterns differ as a function of intervention engagement or baseline stratification levels of suicidal ideation.

Interview data will be analyzed using a rapid qualitative coding analysis, drawing on principles of Framework Analysis [62,63]. This method is well-suited to small samples and time-sensitive evaluations, allowing for systematic and transparent interpretation of participant feedback across key domains [63]. A deductive coding framework will be developed based on the study aims (e.g., app acceptability, usability, engagement, and perceived impact), while remaining open to inductive insights raised by participants. Data will be summarised within NVivo to facilitate cross-case comparisons and identification of common themes and divergent experiences. This approach balances rigour and practicality and is commonly used in applied health and digital mental health research. Analysis will begin once all interviews are completed.

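### Mental health literacy is collected only at T3, so the change-over-time model planned for all secondary outcomes cannot be fitted to it, and H5 can only be tested as a between-group difference at T3

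*Protocol article*

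**What the plan says.** Table 1 states H5 as a comparison of gains: participants using Bud "will report greater increases in mental health literacy from the intervention than the control group". Section 2.9, under Outcomes, gives one schedule for everything: "Primary and secondary outcomes will be assessed at T1, T2 and T3". The same paragraph lists among the secondary outcomes "mental health literacy with the Mental Health Learning Scale (MHL-9 [54]) adapted to refer to the interventions rather than school settings".

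Table 2 also places the 9-item literacy scale under secondary outcomes, but with a single mark, in the T3 column. Its bottom row, "Total # of survey items per group", gives 96 at T1 and 54 at T2 in both groups, and 92 (intervention) and 69 (control) at T3.

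Section 2.10.2 sets one analysis: "Changes in the primary and secondary outcomes will be evaluated using generalised linear mixed models (GLMMs". The model has a participant-level intercept and a time slope as random effects, and group, time and the group-by-time term as fixed effects. The only alternative it mentions is for zero-inflated outcomes such as suicidal ideation. Section 2.10.3 handles missing outcome data by maximum likelihood within those models, with multiple imputation or pattern-mixture models as possible sensitivity analyses if missingness is substantial or departs from missing at random.

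**The concern.** The text and the table give different schedules for one secondary outcome, and the stated model is workable only under the text's version. If Table 2 is right, there is no baseline and no mid-point value. The term that would test a larger gain under Bud, the group-by-time interaction, then does not exist for this outcome.

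The missing-data approach also loses its usual benefit here. For the other secondary outcomes, a participant who skips T3 still contributes T1 and perhaps T2 to the likelihood. For literacy, that participant contributes nothing.

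What is at stake is prespecification. As the protocol stands, the contrast, covariates and missing-data handling for H5 would have to be settled later, in an open-label trial with a self-reported outcome.

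**Working it through.** **Step 1. Which schedule do the totals support?** Inputs are the item counts in Table 2.

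- Baseline only: demographics 14, suicide attempts 2, self-harm 1, CAQ 14, ACEs 11.
- Repeated at each visit: K10 10, GHSQ 12, INQ burdensomeness 5, INQ belonging 5, DERS-SF 18, YSIS-3 3, open feedback question 1.
- Literacy scale: 9.
- T3, both groups: custom acceptability and iatrogenic measure 6.
- T3, intervention group only: funder questions 2, uMARS 20, interview invitation 1.

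| Visit | Sum under the T3-only schedule | Printed total | Sum if the literacy scale were switched |
|---|---|---|---|
| T1 | 14+2+1+14+11+10+12+5+5+18+3+1 = 96 | 96 | 105 (added) |
| T2 | 10+12+5+5+18+3+1 = 54 | 54 | 63 (added) |
| T3 control | 54+9+6 = 69 | 69 | 60 (removed) |
| T3 intervention | 69+2+20+1 = 92 | 92 | 83 (removed) |

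All four printed totals are reproduced exactly with the scale at T3 and nowhere else. A mark lost from the table would not explain this.

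**Step 2. What can the planned model estimate?** With time as three categories, the fixed part has six columns: intercept, group, two time indicators and two group-by-time indicators.

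- Data at T1, T2 and T3: column rank 6 of 6, so all terms are estimable.
- Data at T3 only: column rank 2 of 6. What remains is an overall mean and a group difference.

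Coding time as a continuous variable does not help. At a single visit the time column is a constant multiple of the intercept, and the interaction column is a constant multiple of the group column, so the rank is 2 of 4. A random slope for time needs more than one time point per person. With one record each, a participant intercept in a Gaussian model cannot be separated from the residual.

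**Step 3. What is left, and how precise is it?** The estimable quantity is the difference in mean T3 score between the randomised groups. For context only, assume a two-sided α of 0.05 (section 2.2 gives 0.05 without stating sidedness) and 80 % power, with no covariates. The detectable standardised difference is (1.960 + 0.842) × √(2/n):

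- n = 126 per group, the number in section 2.2 before inflation for attrition: 2.802 × √(2/126) ≈ 0.35.
- n = 120 per group, roughly 302 × 0.80 = 241.6 split in two: 2.802 × √(2/120) ≈ 0.36.

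The T3 comparison is therefore a usable analysis. The inconsistency does not depend on these two figures.

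**The case against.** The strongest reply is that measuring only at T3 is deliberate. Section 2.9 calls the instrument a learning scale and says it was "adapted to refer to the interventions rather than school settings". H5 speaks of gains from the intervention and, unlike H2 to H4, does not mention the post-intervention time point. If the items ask how much participants learned from what they were given, the increase lies in the item content, and a randomised comparison at T3 tests H5 directly. The item wording is not shown, so this can be neither confirmed nor excluded. It stands against the reading that H5 is untestable, which a reader might infer. It does not rescue the schedule stated in section 2.9 or the model stated in section 2.10.2, both of which remain wrong for this scale.

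A reader might also infer that the missing-data plan breaks down. That goes too far. Section 2.10.3 already allows multiple imputation as a sensitivity analysis, though only conditionally. A complete-case regression at T3 is also valid if missingness depends only on group and on the covariates in the model. Nor is the number missing a measure of this flaw: at 20 % attrition about 60 of 302 (302 × 0.20 = 60.4) would lack T3 for every outcome. The 60 % retention boundary in Table 3 is a pilot progression threshold, not an expected T3 loss.

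Finally, an unseen analysis plan may hold outcome-specific detail. That would excuse silence. Here, however, the protocol positively states a schedule and a model that do not fit the outcome.

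**Conclusion.** The point holds as an internal contradiction together with a stated analysis that cannot be applied. Section 2.9 and Table 2 disagree on when literacy is measured, and the item totals settle the matter in favour of T3 only. On that schedule the section 2.10.2 model cannot be fitted, and H5 cannot be tested as change from baseline. The between-group difference at T3 is estimable and, under randomisation, is a valid effect estimate without a baseline value. Under the likelihood approach of section 2.10.3, participants without T3 contribute nothing to this outcome.

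The reach is limited: one of the five secondary hypotheses (H2 to H6), with the primary outcome analysis unaffected. It should be fixed, but it does not threaten the trial. The conclusion assumes that Table 2 describes the surveys as they are actually given.

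**What to change.** 1. Section 2.9: state that the literacy scale is given at T3 only, and limit the three-visit schedule to the other outcomes.
2. Section 2.10.2: exempt this scale from the group-by-time mixed model. Analyse it by regression of the T3 score on group, adjusted for the suicidal-ideation randomisation stratum. Other baseline covariates are optional, but should be named in advance if used.
3. Table 1: restate H5 as a between-group difference at T3 in the intervention-referenced literacy or learning score, and say which of these the adapted items measure.
4. Section 2.10.3: for this outcome, specify multiple imputation of missing T3 scores, using T1 and T2 values of the other outcomes, as a sensitivity analysis.

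The cost is wording in four places, one regression and one sensitivity analysis, with no extra data collection. The price is a weaker claim: a difference at T3 in place of an increase from baseline. Adding the scale at T1 is not an obvious alternative, because items that refer to the intervention may make little sense before participants have seen it.
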